### Secondary outcomes

Physiological, clinical and patient-reported outcomes will be assessed during study visits at baseline, and post-intervention at 4 and 7 months post-randomisation (Table 2).

Exercise capacity will be measured with a graded sub-maximal recumbent cycle ergometer assessment [11]. This will be a simple test (maximum 10 min) involving gradual increments in workload every minute. Workload increments and test termination will be determined by symptoms, heart rate, blood pressure and RPE responses which will be recorded throughout. The increase in heart rate from supine to 10-min stand test (active stand test) will be conducted as per clinical practice [25]. This is a commonly used diagnostic test for POTS, measuring the heart rate response to 10 min (or however long is manageable dependant on symptoms) of standing. It will be performed only as an outcome measure in this trial, not for diagnostic purposes.

The symptom burden of POTS will be measured with the Composite Autonomic Symptom Score (COMPASS 31) dysautonomia scale [26]. This is a self-rating questionnaire evaluating six domains of autonomic function: orthostatic intolerance, vasomotor, secretomotor, gastrointestinal, bladder and pupillomotor domains. In addition to domain scores, an overall total score from 0 to 100 can be computed, with a higher score indicating a greater disease burden. Health-related quality of life will be evaluated with the EQ-5D-5L [27], a validated, generic HRQoL measure consisting of five dimensions, each with five levels of response. It has good test-retest reliability, is simple to use and gives a single preference-based index value for health status. The Fatigue Severity Scale [28], a validated nine-item questionnaire, will be used to assess disabling fatigue. Each item is rated on a seven-point scale, from strongly disagree to strongly agree. A total score is derived from all nine questions; a higher score indicates a greater impact of fatigue on everyday activities. Self-efficacy will be measured with the generalised self-efficacy scale [29] which is a 10-item psychometric scale designed to assess optimistic self-beliefs to cope with a variety of difficult demands in life. A single score between 10 and 40 is generated; greater self-efficacy is represented by a higher score.

To evaluate the participants’ response to exercise sessions and assessments, any POTS-related or associated symptoms will be recorded. Adverse and serious adverse events will be documented and reported to the trial management group (TMG) in accordance with the principles of good clinical practice (GCP).

### Sample size

This is a feasibility RCT to assess recruitment, uptake, adherence, acceptability and clinical, physiological and health-related outcomes. Thus, the sample size is not based on a power calculation. Nevertheless, the aim is to estimate any possible effect of the change of heart rate from supine to 10-min stand between the two treatment arms to inform a future definitive RCT. The sample size is determined using the confidence interval approach to provide a given level of precision. From a single-arm study investigating a 3-month community exercise programme in a similar population [8], the mean increase in heart rate from supine to 10-min stand at baseline was 46 ± 17 bpm and post-intervention was 23 ± 14 bpm. For the purpose of this trial, the standard deviation (SD) is assumed to be the same for both treatment arms, and the SD of the difference of the change is 17 bpm. Therefore, the total sample size required to obtain a 95% confidence interval width of 20 bpm is 46 participants [30]. Assuming a drop-out rate of 25%, the total sample size required is 62 participants (31 per treatment arm). Participants will be randomised equally to the intervention or usual care arms (i.e. 1:1 ratio).

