### Data analysis

Participant demographics and physiological, clinical and patient-reported outcomes will be summarised by treatment arms as mean and SD, median and interquartile range (for continuous data) or frequency and percentage (for categorical data) at baseline, and 4 and 7 months post-randomisation. The primary outcome is feasibility; therefore, process indicators relating to recruitment and intervention delivery will be assessed. Descriptive statistics will be presented by recruitment centre and treatment arm. The difference in outcomes between treatment arms at 4 and 7 months post-randomisation and the difference of the change from baseline to 4 months post-randomisation between arms will be computed. All estimates will be reported with a 95% confidence interval. No formal hypothesis testing will be performed.

All data will be analysed and reported in accordance with the CONSORT statement. All primary analyses are planned on an intention-to-treat basis (i.e. data will be analysed according to the treatment arm the participant was originally allocated to, irrespective of what treatment they actually received) with a secondary per protocol analysis.

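### The 20 bpm precision behind N = 62 holds for a single-visit comparison between arms, but is not established for the baseline-to-4-month change that the 17 bpm label describes

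*Protocol article*

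**What the plan says.** In the protocol article, the Sample size section says that N does not come from a power calculation but from a target precision. The quantity to be estimated is described as follows: "estimate any possible effect of the change of heart rate from supine to 10-min stand between the two treatment arms".

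The only data quoted come from a single-arm study of a community exercise programme: "the mean increase in heart rate from supine to 10-min stand at baseline was 46 ± 17 bpm and post-intervention was 23 ± 14 bpm". The section then makes two assumptions. One is a common SD across the arms. The other sets its value, in these words: "the SD of the difference of the change is 17 bpm". From these it concludes that "the total sample size required to obtain a 95% confidence interval width of 20 bpm is 46 participants", and a 25% drop-out allowance raises this to 62 (31 per arm).

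The Data analysis section plans two kinds of between-arm estimate, each with a 95% interval. One is the difference in outcomes at 4 months and at 7 months. For the other, "the difference of the change from baseline to 4 months post-randomisation between arms will be computed".

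**The concern.** The two source SDs describe the spread of the stand response at one visit each. Neither is the SD of a within-person change between visits, and no pre-post correlation is quoted from which one could be derived. Yet 17 bpm, which equals the baseline SD, appears in the next sentence labelled as an SD for the difference of the change. The Data analysis section uses that same expression for the change from baseline to 4 months compared between arms.

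The SD of a change score depends on the correlation between visits. It can be larger or smaller than the single-visit SD. If the 20 bpm target is meant for the change score, the document does not show that it is met.

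This matters because the interval width is the only numerical basis given for N, and because the section's stated purpose is to inform the definitive trial. A reader planning that trial could take 17 bpm as an established SD of change, which the document does not support.

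**Working it through.** **Inputs** (all from Sample size): two-sided 95% interval; full width 20 bpm, so half-width 10 bpm; SD 17 bpm, equal in both arms; source SDs 17 bpm (baseline) and 14 bpm (post-intervention); 1:1 allocation; drop-out 25%. The pre-post correlation r is not given, so a range is assumed below.

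**1. Reproducing the plan's figures.** For a difference between two means, n per arm = 2 × (z × SD / half-width)².

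- 2 × (1.96 × 17 / 10)² = 2 × 11.10 = 22.2, so 23 per arm and 46 in total.
- 46 / (1 − 0.25) = 61.3, so 62.

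Both figures reproduce. With t quantiles the answer is 24 per arm (48 in total), a negligible difference.

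**2. What 17 bpm must be.** The formula takes a per-arm SD. If 17 were the SD of a difference between one participant in each arm, the per-arm SD would be 17/√2 = 12.0 and n = 11.1, so 12 per arm and 24 in total. That does not give 46. The calculation therefore treats 17 bpm as the per-arm SD of the analysed variable.

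**3. Width for a single-visit comparison.** Width = 2 × q × SD × √(2/n), with SD 17 and n = 23 per arm.

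- z-based: 2 × 1.96 × 17 × √(2/23) = 19.65 bpm.
- t-based (44 degrees of freedom): 20.2 bpm.

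The stated precision holds here without any correlation.

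**4. Width for the change score.** SD(change) = √(s₀² + s₁² − 2·r·s₀·s₁).

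- With s₀ = 17 and s₁ = 14, SD(change) = 17 requires r = 14 / (2 × 17) = 0.41.
- With s₀ = s₁ = 17, it requires r = 0.5.

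With 23 completers per arm:

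| Assumed r | SD of change, 17 and 14 | t-based width | SD of change, 17 and 17 | t-based width |
|---|---|---|---|---|
| 0.2 | 19.7 | 23.5 | 21.5 | 25.6 |
| 0.3 | 18.5 | 22.0 | 20.1 | 23.9 |
| 0.4 | 17.2 | 20.4 | 18.6 | 22.1 |
| 0.5 | 15.7 | 18.7 | 17.0 | 20.2 |
| 0.7 | 12.3 | 14.6 | 13.2 | 15.7 |

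The left-hand pair assumes that the SD falls to 14 at follow-up in both arms. The 14 is a post-exercise figure, and the usual-care arm gets no supervised training, so the right-hand pair is shown as well. The z-based widths are slightly smaller (22.8 rather than 23.5 at r = 0.2 in the first case).

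**5. Width for a baseline-adjusted 4-month difference.** The residual SD is about s₁ × √(1 − r²), which cannot exceed s₁. With s₁ = 17:

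- r = 0.2: 20.2 × √0.96 = 19.8 bpm.
- r = 0.5: 20.2 × √0.75 = 17.5 bpm.

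So the width is about 20 bpm or less whatever the correlation, provided that the follow-up SD is at most 17.

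**The case against.** The strongest reply is that the word change in the Sample size section may mean the rise from supine to standing itself. The stated aim can be read that way. A single-visit SD is then the right input, no correlation is needed, and 46 delivers the claimed width. The Data analysis section does plan such an estimate at 4 and 7 months. This part stands: on that reading the number is sound. It does not settle the matter, because the Data analysis section uses the same phrase for the change from baseline to 4 months. The change estimate would then have no stated precision at all.

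Several stronger readings are tempting, and the document does not support them:

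- **That 17 bpm was copied from the baseline SD.** The protocol does not say so. The two figures are equal and no other source is given, but the origin remains an inference.
- **That the trial is too small.** The error can go either way. Above a correlation of about 0.41 to 0.5 the interval for the change is narrower than promised.
- **That N should have been 24.** The equal-SD assumption and the stated 46 both point to a per-arm SD. The literal reading shows only that the label is loose.
- **That the arithmetic is wrong.** 46 and 62 both follow from 17 bpm.

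It is also fair that this is a feasibility trial with no hypothesis testing, that the trial will yield its own SDs for later use, and that an article may leave the derivation of an assumed SD to the full protocol. These points limit the weight. They do not remove the mismatch among the SD, its label and the target estimate, all of which the article itself states.

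**Conclusion.** The concern holds in a limited form. The calculation is correct for a per-arm SD of 17 bpm, and it supports a width of about 20 bpm for the between-arm difference in the stand response at one visit. It does not establish that width for the baseline-to-4-month change. There the claim needs an unstated correlation of about 0.41 or 0.5, depending on the follow-up SD.

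Over assumed correlations of 0.2 to 0.7, with 46 completers, the t-based width for the change is 23.5 down to 14.6 bpm (SDs 17 and 14) or 25.6 down to 15.7 bpm (SD 17 at both visits). These ranges rest on the assumed correlations and on equal SDs across arms. The paragraph should be corrected, but neither the sample size nor the feasibility objectives are put in doubt.

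**What to change.** Keep N at 62 and reword the paragraph:

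1. Call 17 bpm an assumed per-arm SD of the supine-to-stand rise at one visit, and give its basis.
2. Attach the 20 bpm statement to the 4-month difference between arms, preferably adjusted for the baseline stand-test value, which is already collected. State that the width is about 20 bpm or less if the follow-up SD is at most 17 bpm.
3. If the change score remains the target, state the assumed pre-post correlation and follow-up SD, and show the width over a range, as in the table above.

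This takes one paragraph of rewording and, if the adjusted estimate is adopted, a matching line under Data analysis. No further participants or measurements are needed. The cost is that the stated precision for the change score looks less favourable at low correlations.

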### Data analysis

Participant demographics and physiological, clinical and patient-reported outcomes will be summarised by treatment arms as mean and SD, median and interquartile range (for continuous data) or frequency and percentage (for categorical data) at baseline, and 4 and 7 months post-randomisation. The primary outcome is feasibility; therefore, process indicators relating to recruitment and intervention delivery will be assessed. Descriptive statistics will be presented by recruitment centre and treatment arm. The difference in outcomes between treatment arms at 4 and 7 months post-randomisation and the difference of the change from baseline to 4 months post-randomisation between arms will be computed. All estimates will be reported with a 95% confidence interval. No formal hypothesis testing will be performed.

All data will be analysed and reported in accordance with the CONSORT statement. All primary analyses are planned on an intention-to-treat basis (i.e. data will be analysed according to the treatment arm the participant was originally allocated to, irrespective of what treatment they actually received) with a secondary per protocol analysis.

### Embedded qualitative study

Semi-structured interviews, conducted by an experienced qualitative researcher, with approximately *n* = 10 intervention group and *n* = 10 usual care, at baseline and 4 months post-randomisation (same participants at both time-points), will be digitally recorded, pseudonymised and transcribed verbatim. Data will be analysed using the framework method [31], broadly as follows:
Data familiarisation: reading of complete interview transcripts, listening to original audio recordings and use of field notes;Identifying a thematic framework: key issues, concepts and themes will be identified, and an index of codes developed;Indexing: the index generated through identification of the thematic framework will be applied to all data;Charting: a summary of each passage of text will be transferred into a chart to allow more overall and abstract consideration of index codes across the data set and by each individual;Mapping and interpretation: understanding the meaning of key themes, dimensions and the broad overall picture of the data and identifying and understanding the typical associations between themes and dimensions.

The charting process will provide an opportunity to code data from numerous perspectives. The computer package NVivo will be used to organise the analysis. The findings of the qualitative analyses will be reported as a separate chapter in the final report but will also be incorporated in the discussion to bring together a synthesis of all the results, thus helping to explore and explain the overall ‘value’ of the interventions. Quantitative and qualitative data will be integrated using a mixed methods matrix where quantitative responses can be compared to interview data and recorded on a matrix [32].

### Transition to a definitive trial

The ADePT (A Process for Decision-making after Pilot and Feasibility Trials) framework [33] will be used to identify and examine issues and problems methodically, and to appraise and find appropriate solutions to inform the decision-making process to transition from this two-centre feasibility trial to a definitive multi-centre RCT.

### Data collection and management

Personal data collected during the study will be handled and stored in accordance with General Data Protection Regulation (GDPR). Personal identifying information will be stored at each site for follow-up purposes. Disclosure of confidential information will only be considered if there is an issue which may jeopardise the safety of the participant or another person, in accordance with local standard operating procedures (SOPs) and the UK regulatory framework. An online validated, GCP compliant, electronic data capture system (Castor) will be used by researchers at each site to record and store study data. All data will be pseudonymised after the collection of baseline demographics for each participant. Participants will be assigned a unique study ID, which will be used to identify all documents associated with that participant for the duration of the study. In line with participant consent, direct access to source data/documents will be granted to authorised representatives from the sponsor, host institution and the regulatory authorities, to permit study-related monitoring, audits and inspections.

### Trial monitoring

The trial management group (TMG), chaired by the CI, and consisting of project management staff, lay representatives, co-investigators, the trial statistician and sponsor representatives, will meet monthly for the duration of the project. For this small feasibility RCT, there will be no independent data monitoring committee or trial steering committee; these functions will be completed by the TMG.

### Adverse event management

An adverse event (AE) will be defined as any untoward medical occurrence involving a participant, which does not necessarily have a causal relationship with the intervention or trial. Expected AEs for the PULSE study that will be recorded but not reported include pre-syncope, muscle and joint stiffness, soreness and dislocation and tiredness and fatigue. Any unexpected AEs related to PULSE will be recorded and reported to the TMG. Serious adverse events (SAEs) that have no causal relationship with PULSE will not be reported to oversight committees. Causality and expectedness will be confirmed by the CI with clinician support. SAEs deemed to be unexpected and possibly, probably or definitely related to PULSE will be notified to the Research Ethics Committee (REC) within 15 days. All AEs and SAEs will be recorded within 24 h of the investigator being made aware.

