Primary outcome(s)	Feasibility and process indicators: number of patients screened, eligible, recruited, randomised, withdrawn and retained; adherence to exercise rehabilitation programme; length of time to complete each outcome assessment and the whole outcome assessment appointment; willingness of participants to join non-POTS specific exercise rehabilitation programmes; physiological, clinical, patient-reported outcomes to identify a primary outcome for a definitive trial; acceptability of the interventions and the trial (qualitative interviews)
Key secondary outcomes	At 4 and 7 months: exercise capacity—graded recumbent cycle ergometer test; autonomic function—increase in heart rate from supine to 10-min stand; symptom burden—COMPASS 31 dysautonomia scale and fatigue severity scale; HRQoL—EQ-5D-5L; self-efficacy—general self-efficacy scale; exercise tolerability—continuous heart rate monitoring and symptoms during exercise; adverse events. At baseline and 7 months: semi-structured interviews with participants

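### Two sections of the protocol conflict on which adverse events reach the trial management group, and the narrower one withholds expected AEs and unrelated SAEs from the only monitoring body

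*Protocol article*

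**What the plan says.** Three parts of the protocol article bear on this.

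- **Secondary outcomes** gives a general rule: "Adverse and serious adverse events will be documented and reported to the trial management group (TMG"), following good clinical practice. It makes no exception for expectedness or causality. It also has POTS-related symptoms recorded at exercise sessions and at assessments.
- **Adverse event management** defines an AE without regard to cause, as "any untoward medical occurrence involving a participant, which does not necessarily have a causal relationship with the intervention or trial", and then sets narrower reporting rules. Expected events: "Expected AEs for the PULSE study that will be recorded but not reported include pre-syncope, muscle and joint stiffness, soreness and dislocation", with tiredness and fatigue added. Other AEs: "Any unexpected AEs related to PULSE will be recorded and reported to the TMG". Unrelated serious events: "Serious adverse events (SAEs) that have no causal relationship with PULSE will not be reported to oversight committees". Ethics notification: "SAEs deemed to be unexpected and possibly, probably or definitely related to PULSE will be notified to the Research Ethics Committee (REC) within 15 days". The recording rule has no filter: "All AEs and SAEs will be recorded within 24 h of the investigator being made aware".
- **Trial monitoring** provides for no independent data monitoring committee or steering committee. The TMG takes on both functions and meets monthly.

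Adverse events are also an outcome. The key secondary outcomes in Table 1, at 4 and 7 months, end with "symptoms during exercise; adverse events".

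**The concern.** Staff cannot follow both rules. If they follow Adverse event management, the only body charged with monitoring would not see how often the foreseen harms of exercise occur. Joint dislocation is the clearest case. The Safety section provides specialist physiotherapy training to help avoid it in hypermobile participants, and the Background calls hypermobility a common comorbidity, yet dislocation is on the list of events not reported. An event being expected does not make any frequency of it acceptable, and frequency is what a monitoring body needs.

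A second issue concerns the final comparison. Only the intervention arm attends supervised sessions, where symptoms are recorded. A by-arm table of everything recorded would therefore mix any true difference in harm with a difference in how often events could be noticed.

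**Working it through.** The protocol gives no figure to reproduce on this point. The check sets the reporting rules side by side and then counts contacts.

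**Step 1: routing to the TMG.** Events are classed by seriousness, expectedness and relatedness, which gives 2 × 2 × 2 = 8 classes. Under Secondary outcomes all eight go to the TMG. Under Adverse event management:

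| Class | To the TMG under Adverse event management? |
|---|---|
| Non-serious, unexpected, related | Yes |
| Non-serious, unexpected, unrelated | No route stated |
| Non-serious, expected, related | Not reported |
| Non-serious, expected, unrelated | Not reported |
| Serious, unexpected, related | Yes, if an SAE counts as an AE; also to the ethics committee |
| Serious, expected, related | No route stated; not expressly withheld |
| Serious, unexpected, unrelated | Withheld from oversight committees |
| Serious, expected, unrelated | Withheld from oversight committees |

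The two sections agree on 2 of the 8 classes. In 4 the narrower section withholds the event, and in 2 it is silent. Reading the TMG as an oversight committee is an inference, but a firm one, because Trial monitoring names no other committee with that function.

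**Step 2: recording.** The 24-hour rule covers all AEs and SAEs, and the AE definition does not depend on cause. The filter therefore acts on who is told during the trial, not on what is in the database.

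**Step 3: opportunity to record events before and at follow-up.**

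- Intervention arm: one to two sessions per week. Table 2 gives 8 to 12 weeks; the programme description gives 12. Lowest count 1 × 8 = 8; highest 2 × 12 = 24.
- Control arm: 1 practitioner session, then no further input in the control period.
- Both arms: 2 follow-up visits (4 and 7 months).
- Behavioural sessions take place next to a supervised session, so they are not counted again.

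Ratio including follow-up visits: (8 + 2)/(1 + 2) = 3.3 to (24 + 2)/(1 + 2) = 8.7. Counting the intervention arm's individual assessment as one more contact gives (8 + 1 + 2)/3 = 3.7 to (24 + 1 + 2)/3 = 9.0.

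**Step 4: masking.** Under Randomisation, allocation concealment and blinding, the chief investigator and trial statistician stay blinded until analysis is complete. Under Trial monitoring, the former chairs the TMG and the latter is a member. Routine by-arm tables to the full TMG would break that blinding, which limits the form a remedy can take.

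**The case against.** The best defence is that the phrase about expected events names no recipient and may refer only to expedited reporting, so that the general rule in Secondary outcomes still governs what the TMG sees. This is possible but strained: the next sentence names the TMG as recipient of a narrower class of AEs, and the rule on unrelated SAEs names oversight committees outright. At the least, the text does not settle the matter.

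Other parts of the defence stand, and they rule out stronger readings that a reader might be tempted to make:

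- *That the TMG would never see these harms.* This needs the narrower section to override the general one, and the protocol does not say which prevails. Related but expected SAEs are not expressly withheld. Pre-syncope is on the list; syncope is not.
- *That harms cannot be compared between arms.* All events are recorded and AEs are a listed outcome. Nothing says that expected events are dropped from the final tables.
- *That relatedness can arise only in the exercise arm.* Both arms undergo the cycle test and the active stand test, either of which could cause a trial-related event in a control participant.
- *That contact differs at least 12-fold.* Table 2 allows 8 weeks, and both arms share the follow-up visits.

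It is also fair to say that unequal contact is inherent in comparing supervised exercise with usual care, that the way AEs are elicited may be set out in the full protocol, and that this is a 62-person feasibility trial without hypothesis tests, run in units with qualified staff. These points limit the weight of the finding but do not remove the conflict.

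**Conclusion.** The contradiction is real. On its literal reading, Adverse event management keeps non-serious expected AEs (including dislocation) and unrelated SAEs from the only monitoring body, and it leaves related but expected SAEs without a stated route there. The consequence is weaker safety oversight during the trial, not a loss of data.

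The between-arm comparison remains possible but is exposed to ascertainment bias: about 8 to 24 supervised sessions against 1 control session before the 4-month visit, or roughly 3- to 9-fold once shared visits are counted. That range assumes full attendance and that each contact is one opportunity to record an event. It does not measure the bias itself, for which the protocol gives no basis.

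The point should be settled before recruitment starts; Trial status says that it had not begun.

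**What to change.** 1. Reconcile the two sections. State that the TMG periodically receives all recorded AEs and SAEs, whatever their expectedness or causality.
2. Present that listing pooled across arms. If a by-arm version is wanted, restrict it to an unblinded reader, so that the chief investigator and trial statistician stay blinded.
3. Leave the expedited ethics committee criteria as they are.
4. In the final report, tabulate all recorded AEs and SAEs by allocated arm.
5. Ask both arms the same AE question at the 4- and 7-month visits, base the between-arm comparison on those answers, and list events recorded at supervised sessions separately.

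The cost is revised wording, one extra TMG listing that can go to the monthly meetings, and a short question at visits already planned. The sample size and the intervention do not change.
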